# The effect of transcranial direct current stimulation (tDCS) on locomotion and balance in patients with chronic stroke: study protocol for a randomised controlled trial

**DOI:** 10.1186/s13063-017-2219-6

**Published:** 2017-10-23

**Keywords:** Stroke, Transcranial direct current stimulation, Gait, Motion analysis, Balance

## Abstract

**Background:**

Following stroke, patients are often left with hemiparesis that reduces balance and gait capacity. A recent, non-invasive technique, transcranial direct current stimulation, can be used to modify cortical excitability when used in an anodal configuration. It also increases the excitability of spinal neuronal circuits involved in movement in healthy subjects. Many studies in patients with stroke have shown that this technique can improve motor, sensory and cognitive function. For example, anodal tDCS has been shown to improve motor performance of the lower limbs in patients with stroke, such as voluntary quadriceps strength, toe-pinch force and reaction time. Nevertheless, studies of motor function have been limited to simple tasks. Surprisingly, the effects of tDCS on the locomotion and balance of patients with chronic stroke have never been evaluated. In this study, we hypothesise that anodal tDCS will improve balance and gait parameters in patients with chronic stroke-related hemiparesis through its effects at cortical and spinal level.

**Methods/design:**

This is a prospective, randomised, placebo-controlled, double-blinded, single-centre, cross-over study over 36 months. Forty patients with chronic stroke will be included. Each patient will participate in three visits: an inclusion visit, and two visits during which they will all undergo either one 30-min session of transcranial direct current stimulation or one 30-min session of placebo stimulation in a randomised order. Evaluations will be carried out before, during and twice after stimulation. The primary outcome is the variability of the displacement of the centre of mass during gait and a static-balance task. Secondary outcomes include clinical and functional measures before and after stimulation. A three-dimensional gait analysis, and evaluation of static balance on a force platform will be also conducted before, during and after stimulation.

**Discussion:**

These results should constitute a useful database to determine the aspects of complex motor function that are the most improved by transcranial direct current stimulation in patients with hemiparesis. It is the first essential step towards validating this technique as a treatment, coupled with task-oriented training.

**Trial registration:**

ClinicalTrials.gov, ID: NCT02134158. First received on 18 December 2013; last updated on 14 September 2016. Other study ID numbers: P120135 / AOM12126, 2013-A00952-43.

**Electronic supplementary material:**

The online version of this article (doi:10.1186/s13063-017-2219-6) contains supplementary material, which is available to authorized users.

## Background

Stroke is the primary cause of morbidity and the third cause of mortality (50,000 deaths per year) in industrialised countries. Stroke causes multiple impairments, including motor deficits, with a loss of voluntary movement, abnormal movements and changes in muscle tone that reduce balance and alter gait [1, 2]. Postural symmetry is altered, as indicated by changes in the position and stability of the centre of pressure (COP). Studies using force platforms have demonstrated an increase in postural oscillations, as well as a shift of the COP towards the non-hemiparetic limb (asymmetry of weight distribution) [3–7]. Eng and Chu (2002) showed that 79 to 87% of patients with hemiparesis support less weight through their hemiparetic limb (25 to 43% of body weight) [8]. Nardone et al. (2009) found a relationship between the degree of postural asymmetry measured by stabilometry and gait capacity [9]. Moreover, it has been shown that postural control and static equilibrium following stroke directly influence spatiotemporal gait parameters. For example, gait velocity in patients with hemiparesis has been shown to relate to the quality of static equilibrium, weight transfer capacity towards the hemiparetic limb and weight distribution between the limbs during gait [1]. There is also a relationship between gait efficacy measured by the Motor Assessment Scale and the degree of weight transfer on the hemiparetic limb [10]. Interestingly, patients with hemiparesis limit the velocity and amplitude of their movements, inducing internal perturbations of posture [5].

As well as impairing balance, stroke alters gait. Patients with stroke typically have: (1) altered kinematics including reduced hip flexion, knee flexion, hip extension, increased knee extension during stance and reduced ankle dorsiflexion during swing [11–13] and (2) spatiotemporal changes such as asymmetry in the duration of support and swing phases between the two legs [10, 12, 14, 15], reduced gait speed, stride length and cadence [1, 11, 16]. These disorders are mainly due to paresis and spasticity, especially spasticity of the rectus femoris and triceps surae muscles [12, 17]. Currently, three-dimensional (3D) gait analysis is the ‘gold standard’ method to quantify gait parameters and to guide treatment [16, 18–22]. This technique consists of simultaneously quantifying spatiotemporal, kinematic and kinetic gait parameters. In addition, the displacement of the centre of mass (COM) during gait can also be evaluated [23], providing useful information regarding the control of gait [23–25]. Studies of the displacement of the COM in patients with hemiparesis [23, 24] have shown that its displacement is altered compared with healthy subjects, who have stereotypical trajectories.

The primary motor cortex (M1) and the cortico-spinal tract play a greater role in the control of locomotion in humans than in other mammals. Many studies suggest that gait is accompanied by an increase in cortical activity [26, 27]. Several authors have demonstrated that during gait, cortico-spinal neurone activity occurs in parallel with, or perhaps partially controls, the activity of spinal motoneurones [28–30]. In patients with hemiparesis, Dobkin et al. (2004) showed a relationship between improvements in gait and activation capacity of the different cortical areas representing the lower-limb muscle groups involved in gait [31]. Therefore, any method that facilitates activation of the cortical neurones at the origin of the descending tracts that control the spinal motoneurones of the hemiparetic limb (final common pathway) could improve motor performance in patients with cortical or subcortical lesions causing gait and balance impairments.

Transcranial direct current stimulation (tDCS) was developed in humans by Priori in 1998 and by Nitsche and Paulus in 2000 [32, 33]. The latter authors showed that, when applied over the motor cortex, tDCS modifies cortical excitability depending on the polarity used. When the anode is placed over the motor cortical area to be stimulated, and the cathode above the contralateral eye, tDCS (thus termed anodal) increases cortical excitability, both during and following the stimulation, demonstrated by an increase in the amplitude of the motor-evoked potential (MEP) generated by TMS. Conversely, when the cathode is placed over the motor cortical area to be stimulated, and the anode above the contralateral eye, cortical excitability is reduced. Moreover, the effects of tDCS persist after the stimulation (named post effects) [33]. The duration of the post effects depends on the duration and intensity of the stimulation [32, 33]. Furthermore, tDCS is safe, easy to use, well tolerated, and has minor side effects such as (1) a sensation of itching under the stimulating electrode, (2) post-stimulation headache and (3) mild nausea, which is rare [34].

The effects of tDCS are not limited to the motor cortex below the stimulating electrode. During stimulation, anodal tDCS also induces changes in the excitability of spinal neuronal circuits [35–37]. Roche et al. (2011, 2012) showed that 20 min of anodal tDCS increased homonymous recurrent inhibition on the α motoneurones of the soleus muscle during the stimulation [36], and decreased lumbar propriospinal facilitation [37] during and after cessation of the cortical stimulation in healthy subjects. However, cathodal tDCS did not modify the excitability of spinal neuronal circuits [36, 37]. Jeffery et al. (2007) also found that anodal tDCS over the area of the tibialis anterior increased cortical excitability in healthy subjects (evaluated using TMS) [38] while cathodal tDCS did not. Anodal tDCS over the M1 leg area (1 mA for 20 min) has been shown to improve dynamic balance compared with a placebo condition [39], as well as reducing reaction time and increasing toe-pinch strength in healthy subjects [40]. Tanaka et al. (2009) thus concluded that anodal tDCS would be a useful tool for the neurorehabilitation of patients with motor disorders of the lower limbs [40].

The results of these different studies strongly suggest that anodal tDCS is a more appropriate stimulation configuration than cathodal tDCS to improve complex motor tasks, such as gait and balance in stroke patients, since it increases cortical excitability and modifies spinal circuit excitability, improving balance [41] and preventing abnormal muscle activation during gait [42]. Indeed, Katz and Pierrot-Deseilligny (1982) showed that during low intensity contractions of the soleus muscle, homonymous recurrent inhibition of the motoneurones did not increase as much as in healthy subjects [41]. Since anodal tDCS increases homonymous recurrent inhibition on the α motoneurones of the soleus muscle [36], it might improve static balance. Marque et al. (2001) showed that the excitability of the lumbar propriospinal system is abnormally increased on the hemiparetic side [42]. They suggest this increased excitability may be the cause of inappropriate activity of the quadriceps muscle during gait, thus theoretically, tDCS should improve gait in patients with hemiparesis by decreasing abnormal muscle activities.

This hypothesis is in accordance with previous results in stroke patients. Chang et al. (2015) found improvements in the lower-limb subscale of the Fugl-Meyer Assessment and the lower-limb Motricity Index after 10 sessions of anodal tDCS (2 mA for 10 min) over 2 weeks, but not in the Functional Ambulatory Category, Berg Balance Scale or spatiotemporal gait parameters [43]. Tanaka et al. (2011) found that anodal tDCS (2 mA for 10 min with the anode placed above the hemiparetic lower-limb M1 representation) significantly increased quadriceps strength in the paretic limb during the stimulation, compared with a placebo condition [44].

In patients with chronic stroke, only two case studies have recently been reported. Dumont et al. (2015) showed that a single session of tDCS (2 mA for 20 min) combined with treadmill training improved static balance in a patient 4 years after the stroke [45]. This case study is interesting; however, since there was no placebo condition, it is difficult to determine the respective contributions of the anodal tDCS and the treadmill training on the improvement in static balance. Nevertheless, this result constitutes an argument for further study of the effects of anodal tDCS on balance in patients with chronic stroke. The second case study of a patient 1 year post stroke showed that repeated sessions (five consecutive days for 3 weeks) of anodal tDCS (2 mA for 20 min) combined with functional electrical stimulation improved performance of the 10-m Walking Test and the Timed Up and Go Test (TUG) [46].

The results of these studies suggest that tDCS may be a useful treatment for patients with subacute and chronic stroke; however, the methodologies are highly variable. In some studies, tDCS is combined with an interventional technique such as treadmill training, rehabilitation or functional electric stimulation; sometimes it is administered for a single session, and sometimes repeated sessions. Moreover, although the case studies are interesting, they do not constitute proof of the effectiveness of anodal tDCS on locomotion and static balance in patients with chronic stroke. Therefore, we plan to accurately assess the effects of a single session of anodal tDCS versus placebo on locomotion and static balance in chronic stroke patients, in order to provide robust information regarding the possible impact of anodal tDCS on locomotion following stroke.

As mentioned above, since the activity of the corticospinal neurones from the M1 motor cortex that control movement of the lower limb increases during gait, we hypothesise that anodal tDCS will improve gait and balance parameters in patients with hemiparesis by increasing cortical excitability both during and after stimulation, and modifying the excitability of spinal circuits mainly during stimulation.

The main aim of this randomised controlled trial is, therefore, to show that a single session of anodal tDCS can decrease the variability of the displacement of the COM during gait, during a static-balance task and during a gait-initiation and obstacle-crossing task in patients with chronic stroke. According to Bikson et al. (2013), tDCS specifically enhances the task performed during the stimulation [47]. Therefore, we will assess the primary outcomes before, during and after the tDCS.

The secondary objectives are:Firstly, to show that compared to placebo condition, anodal tDCS improves spatiotemporal, kinematic and kinetic gait parameters, as well as the ability to follow a trajectory or cross an obstacleSecondly, to show that, compared to a placebo condition, anodal tDCS improves performance on functional tests and clinical tests (assessment of strength and spasticity) that will be not performed during the stimulation. This will determine whether anodal tDCS only improves tasks executed during the stimulation, or if the effects can transfer to other tasks (for example, the paretic upper limb)Thirdly, to show if changes induced by anodal tDCS are correlated with the patient’s profile (based on clinical evaluation scales, performance on functional tests and the time since lesion onset)

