## Method/design

### Study design

This is a prospective, randomised, placebo-controlled, cross-over, double-blind, single-centre study over a period of 36 months.

Each patient included will participate in three visits.

Visit 1 (V1): inclusion and baseline assessment visit. Patients who fulfil all the inclusion and non-inclusion criteria and who have signed informed consent will be included in the study. During this visit, all the clinical and functional evaluations, the instrumented gait analysis and instrumented balance task will be carried out. The patient will also complete all the clinical scales and self-evaluation questionnaires. Furthermore, blood samples will be taken in order to carry out genetic studies and identify carriers of the Val66Met polymorphism in the brain-derived neurotrophic factor gene, since Val66Met reduces the effects of all types of non-invasive brain stimulation [48, 49].

Visits 2 and 3 locomotion/balance (V2 and V3): anodal tDCS or placebo visits. During these visits, before the cortical stimulation (anodal or placebo), all the functional and clinical data will be collected. A 3D gait analysis and instrumented balance task will be carried out before and during the 30 min of stimulation, as well as immediately after the end of the stimulation and 30 min later. Functional and clinical data will be collected again following the stimulation. The order of the placebo and anodal tDCS visits will be randomised. The visits will be 7 days apart. The study schedule is shown in Fig. 1 and the evaluations conducted during the three visits are shown in Table 1.

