### Secondary outcomes

#### Before, during, immediately after and 30 min after tDCS cessation

The same 3D gait analysis described above will be used to evaluate the effect of anodal tDCS on kinematic and kinetic gait parameters, trajectory tracking and obstacle crossing.Gait analysis:

Ten trials of gait at a comfortable speed and 10 trials at maximal speed will be recorded in order to evaluate the spatiotemporal, kinematic, kinetic and EMG parameters during gait. Surface EMG will also be performed during the gait analysis. These data will be used to define the patterns of activation of the principle superficial muscles (rectus femoris, vastus lateralis, medial hamstring, biceps femoris, tibialis anterior, medial gastrocnemius and soleus) activated during gait. The EMG data will be used to quantify the activity of the agonist and antagonist muscles (of the hip, the knee and the ankle) in order to determine a possible interaction between muscle activity, variability of COM displacement and joint kinematicsInstrumented path-following task (trajectory tracking)

From a standing start, the patient will be asked to follow a 2.5-cm-wide strip on the ground, walking with one foot on each side of the strip. The 8-m-long strip will be positioned so as to form a figure of 8. The distance of the trajectory of the COM during this task, as well as its oscillations with respect to the strip, will be quantified. The trajectory length and COM oscillations before, during, immediately after and 30 min after cessation of stimulation will be compared to determine whether the patients’ dynamic stability during the task has been modified by the tDCSInstrumented evaluation of obstacle crossing

From a standing start with one foot on a force platform, the patient will be asked to step over an 11-cm-high, 2-m-wide bar leading with the paretic limb (three trials) and the non-paretic limb (three trials). The time to cross the obstacle, the number of contacts with the obstacle and the height of the foot relative to the obstacle will be determined, as well as the trajectory of the centre of pressure (COP) until the foot is lifted. The patient will be asked to stand still after crossing the obstacleBefore and after the tDCS: clinical evaluation

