Passive range of motion (manual goniometer) of the hip, knee and ankle joints of the hemiparetic lower limb, spasticity (modified Ashworth Scale) and muscle strength (Medical Research Council) of the hip, knee and ankle flexor and extensor muscles of the hemiparetic lower limb will be evaluated before and after stimulation. Functional gait and balance scales and functional tests will also be evaluated (described below) before and after stimulationFunctional clinical tests

Four functional clinical tests of gait and balance will be evaluated: the time to ascend and descend a flight of ten 11-cm-high stairs; the Timed Up and Go Test that evaluates postural transitions, gait, balance, turn-around and risk of falls; the Ten-metre Timed Walk that evaluates gait speed will be carried out at maximal speed; and the 6-minute Walk Test that evaluates the distance walked in 6 min, providing an indication of endurance capacityTests to verify if the upper limb is affected by anodal tDCS

The Box and Block test evaluates unilateral gross manual dexterity. It will be carried out in order to verify if the effects of the stimulation are limited to the motor tasks carried out during the stimulation or also occur in similar tasks such as functional tests (mentioned above) or tasks carried out by another limb.

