## Discussion

### Impact

Comparison of the effects of anodal and placebo tDCS on the different motor functions should demonstrate that anodal tDCS significantly improves gait and balance in chronic stroke by reducing the variability of the COM during gait, static and static-dynamic balance tasks. This study should demonstrate that anodal tDCS improves kinematic and kinetic gait parameters, and performance on functional tests, and reduces the clinical symptoms of stroke (reduced spasticity and increased strength). We will also determine: (1) if the changes induced by anodal tDCS are correlated with the patient’s level of function according to the clinical evaluation scales and (2) if there is a relationship between functional performance and improvements following anodal tDCS and the time since lesion. Moreover, comparison of the effects of tDCS over time will allow the kinetics of action of the stimulation to be determined. Furthermore, since each task is evaluated by several different methods, the comparison of the effects of anodal tDCS on the task carried out during the stimulation with a similar task not tested during the stimulation will determine if the effects of tDCS on a motor task are potentialised by the practice of a task during stimulation as suggested by Bikson et al. (2013) [47]. However, if the results show that tDCS has no effect on the variables analysed, the comprehensive data collection will allow analysis of whether the lack of effects depends on the profiles or the level of performance of the patients. If no robust explanation is found, this would suggest that anodal tDCS has no effect on gait and balance. In this case, further studies should investigate other stimulation conditions (bilateral stimulation, stimulation of another cortical zone of or repeated stimulations sessions). The analysis of the different Val66Met profiles could also provide explanations regarding a lack of effect.

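### Maximal-speed walking is practised during stimulation, so a gain on the maximal Ten-metre Timed Walk is not evidence of transfer, and the design cannot determine whether practice potentiates tDCS

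*Protocol article*

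**What the plan says.** The Background of the protocol article gives the premise that "tDCS specifically enhances the task performed during the stimulation". The second secondary objective then covers functional and clinical tests "that will be not performed during the stimulation. This will determine whether anodal tDCS only improves tasks executed during the stimulation", the alternative being that effects carry over to other tasks. Its example of such a task is the paretic upper limb.

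Under Study design, "A 3D gait analysis and instrumented balance task will be carried out before and during the 30 min of stimulation". The Primary outcomes section, whose heading includes the period during stimulation, gives the content of the gait task: "Ten trials of gait at a comfortable speed and 10 trials at maximal speed will be recorded". The Secondary outcomes section repeats this under a heading with the same time points: "Ten trials of gait at a comfortable speed and 10 trials at maximal speed will be recorded in order to evaluate" spatiotemporal, kinematic, kinetic and EMG parameters.

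The functional clinical tests, done before and after stimulation, are the stairs, the Timed Up and Go, the Ten-metre Timed Walk and the 6-minute Walk. Of these, "the Ten-metre Timed Walk that evaluates gait speed will be carried out at maximal speed". The paragraph on the Box and Block test asks whether effects are confined to tasks carried out during stimulation or "also occur in similar tasks such as functional tests (mentioned above) or tasks carried out by another limb".

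The Impact section of the Discussion says that comparing the task carried out during stimulation with a similar one not tested during it "will determine if the effects of tDCS on a motor task are potentialised by the practice of a task during stimulation".

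**The concern.** The transfer objective needs a clean division between tasks executed under stimulation and tasks that are not. The protocol draws that line by test name: the functional tests are not run during stimulation, so they count as not executed. Drawn by activity, the line falls elsewhere, because walking at maximal speed is done during stimulation and is also what the Ten-metre Timed Walk measures. On the protocol's own premise of task specificity, a Ten-metre Walk gain is the effect expected on a practised activity. Read as the objective is worded, the same gain would count as transfer.

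The Impact statement goes further and promises to settle whether practice during stimulation enhances the effect. That is a claim about an interaction between practice and tDCS, and the trial does not vary practice. At stake are the conclusion of one secondary objective and a mechanistic statement in the Discussion.

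**Working it through.** No figure in the plan bears on this point, so there is none to reproduce. The check has three parts.

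**1. Which activities are executed during stimulation.** Study design, Primary outcomes and Secondary outcomes list four gait assessments per stimulation visit (before, during, immediately after, 30 min after), each with 10 maximal-speed trials:

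- maximal-speed trials per stimulation visit: 4 × 10 = 40
- of these, during stimulation: 1 × 10 = 10

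The same headings also place comfortable-speed gait, quiet standing, step initiation, path following and obstacle crossing in the period during stimulation. Set against the tests done only before and after:

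| Test | Counterpart during stimulation | Overlap |
|---|---|---|
| Ten-metre Timed Walk, maximal | 10 maximal-speed gait trials | Essentially the same activity |
| Timed Up and Go | Gait, step initiation, figure-of-8 path | Partial; it adds postural transitions and a turn-around |
| 6-minute Walk | Gait trials | Partial; it measures endurance |
| Stairs (11-cm steps) | Crossing an 11-cm bar | Possible |
| Strength, spasticity | None | None |
| Box and Block | None | None |

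**2. Whether a practice effect can be estimated.** Take 11 tasks under 2 conditions (anodal, placebo). Six are executed during stimulation: maximal gait, comfortable gait, quiet standing, step initiation, path following, obstacle crossing. Five are not formally run then: Ten-metre Walk, Timed Up and Go, 6-minute Walk, stairs, Box and Block. The model is

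response = task effect + (task-specific tDCS effect) × anodal + γ × practised × anodal

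- Columns: 11 task effects + 11 task-specific tDCS effects + 1 practice term = 23.
- The practice column equals the sum of the six tDCS columns of the practised tasks, because practice status depends only on task.
- Rank with the practice term is 22; without it, also 22.

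So γ is not identified. Moving the Ten-metre Walk to the practised group leaves this unchanged, since practice is still a function of task. Separating γ would require assuming that all tasks and their measures respond equally to tDCS, although they are recorded as COM variability, seconds, metres and block counts. Using only pairs of similar tasks reduces those differences but does not remove the confounding.

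**3. A caution on comparing significance.** This is an illustration, not a rule in the plan. Assume a paired standardised effect of d = 0.5 on two outcomes; the protocol gives no such value. With n = 39 (the calculated sample size) and a two-sided 5% test, a paired t test has power 0.86. If the two results are independent,

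P(exactly one significant) = 2 × 0.86 × (1 − 0.86) = 2 × 0.86 × 0.14 = 0.24.

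Outcomes in the same patients are likely to be correlated. By simulation, correlations of 0.3, 0.5 and 0.7 between the paired differences give about 0.21, 0.18 and 0.14. With identical true effects, one outcome would therefore be significant and the other not in roughly 14 to 24% of trials.

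**The case against.** The quoted objective is literally correct: the functional tests are collected before and after stimulation and never during it. The protocol also grades task distance to some extent, distinguishing tasks carried out during stimulation, similar tasks and tasks of another limb, and its own example of transfer is the arm. The Timed Up and Go and 6-minute Walk contain elements that no recorded gait trial contains. All of this stands. It limits the point to how an activity is classified and does not show that the tests are scheduled wrongly. It does not rescue the Ten-metre Walk, which the objective still places among the tests used to judge transfer.

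Three stronger readings are tempting, and the document does not support them:

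- A reader might infer that the transfer objective fails altogether. It does not: Box and Block, strength and spasticity have no counterpart during stimulation, and anodal versus placebo on them remains interpretable.
- A reader might infer that the Impact section plans to set COM variability against Box and Block. It speaks of a similar task, which Box and Block is not.
- A reader might infer that specificity will be judged by one p-value being significant and another not. The Statistical analysis section states no such rule, so the 14 to 24% above is a general caution and not an error rate of this plan.

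It can also be said that grouping secondary outcomes belongs in a full protocol or SAP. That is fair for the classification of the tests. It does not cover the Impact claim, because no analysis of these data can supply a contrast that the design lacks.

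**Conclusion.** The point holds as a minor one on a secondary objective. A gain on the maximal-speed Ten-metre Timed Walk cannot be read as transfer to a task not executed during stimulation, because 10 maximal-speed walking trials take place in that period. The overlap is partial for the Timed Up and Go and 6-minute Walk and possible for the stairs. The statement that the trial will determine whether practice potentiates tDCS is not supported, because practice never varies within a task and is fully confounded with task and measure.

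The first conclusion rests on judging a timed maximal walk and a recorded maximal-speed gait trial to be the same activity. The second rests only on the two-condition design and not on any assumed effect size. The primary outcome and the anodal-versus-placebo comparison on every individual outcome are untouched.

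**What to change.** 1. Class the Ten-metre Timed Walk as a practised task and the Timed Up and Go and 6-minute Walk as near-practised. Note the possible overlap of the stairs with obstacle crossing.
2. Base transfer statements on outcomes with no counterpart during stimulation: Box and Block, strength and spasticity. State that a null result on Box and Block is ambiguous, since it may mean no transfer between tasks or that the stimulation does not affect the arm's motor representation.
3. Report each outcome as a standardised anodal-minus-placebo difference with a 95% confidence interval, side by side, and do not contrast p-values.
4. In the Impact section, restate the practice comparison as exploratory, and say that practised and unpractised tasks also differ in content and measure.

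This is wording plus a small presentation of data already to be collected, with no added visits, patients or measurements. The downside is that the transfer claim rests on fewer outcomes.
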